## 3.10. Data management

Data is initially collected onto the HUGO HEALTH platform with participant permission. Intermittently, data will be pulled and shared with the analytic core at Yale University.

## 3.11. Data monitoring

### 3.11.1. Interim analysis

Periodic reports of de-identified data from participants at each site are exported from the Hugo data management system for monitoring and analysis by the study cores. These data will be used to monitor the adequacy of recruitment, with due consideration to the balance of subjects with positive versus negative tests as well as their age distribution, and completeness of follow-up questionnaires.

## 3.12. Reporting

The results of this study will be reported using the STrengthening the Reporting of OBservational studies in Epidemiology (STROBE) guidelines for reporting observational studies [[44]](https://www.spiritprotocol.com/api/docx/https://paperpile.com/c/nKRweq/ohVFp). We intend to disseminate the results as rapidly as possible to help contribute to the COVID-19 response.

## 3.13. Research partnership

This research will benefit from the contributions of a Patient Advisory Board. This group provides valuable perspective and guides our research team on issues pertaining to participant engagement, survey data collection, and will assist with interpretation of study findings and communicating results to the general population. Additionally, this study is conducted in collaboration with colleagues from the CDC. Scientists from the CDC assisted with study design and will remain engaged as we evaluate and disseminate the research findings.

## 3.14. Participant timeline

Figure 1. Participant Timeline

|  | Enrolment | Post-enrollment |  |  |  |  |  | Close-out |
| --- | --- | --- | --- | --- | --- | --- | --- | --- |
| TIMEPOINT | 0 | 3 mos. | 6 mos. | 9 mos. | 12 mos. | 15 mos. | 18 mos. | tx |
| ENROLLMENT: |  |  |  |  |  |  |  |  |
| Eligibility screen | X |  |  |  |  |  |  |  |
| Informed consent | X |  |  |  |  |  |  |  |
| ASSESSMENTS: |  |  |  |  |  |  |  |  |
| Age, gender, symptoms of SARS-COV-2 infection, recent health care use, social determinants of health | X |  |  |  |  |  |  |  |
| Outpatient visit, emergency department visit, hospitalization, intensive care stay, death, physical and mental health (PROMIS-29), cognitive SF-8, hospital-free survival, intensive care-free survival, dyspnea, cough, exercise, social determinants of health, work and activity status, myalgic encephalomyelitis/chronic fatigue syndrome |  | X | X | X | X | X | X | X |
| Preexisting conditions |  | X | X | X | X |  |  | X |

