## 3.9. Statistical methods

### 3.9.1. Outcomes

Statistical analyses will describe disease course and outcomes, including the characterization of specific symptoms and duration of symptoms, health care utilization (emergency department, hospitalization, post-acute care) with clinical (morbidity/mortality) and patient-reported health status outcomes as well as recovery (early and late disease sequelae). Baseline and demographic characteristics will be summarized by descriptive summaries (e.g., means and standard deviations for continuous variables such as age and percentages for categorical variables such as gender, medians, and quartiles for skewed data). Analyses will:

- Compare health status at baseline and follow-up between persons in the same age group who test SARS-CoV-2 positive and negative at initial test.
- Characterize health care utilization (ambulatory and ED visits, hospitalizations, post-acute care, telehealth visits) among SARS-CoV-2 positive participants by age and compare these to SARS-CoV-2 negative participants.
- Characterize and compare health outcomes by age and SARS-CoV-2 status: emergency or ambulatory care, admission to hospital); ICU-free survival;^16^ hospital-free survival; and subsequent patient-reported health status (cognition; physical health; mental health; and return to work).

We will use statistical modeling to estimate the association between key covariates and outcomes, including evaluating interactions by age. We plan to use survival analysis techniques to analyze time to outcome events, logistic regression for binary outcomes (e.g., hospitalization versus no hospitalization), Poisson or Cox regression for count data (e.g., number of hospitalizations over time), and linear regression models for continuous outcomes (e.g., PROMIS-29). Multiple imputation will be considered to handle missing covariate and outcome data in these analyses [[43]](https://www.spiritprotocol.com/api/docx/https://paperpile.com/c/nKRweq/3dpny). Chained equations will be used to impute each variable with missing data. Sensitivity analyses will be conducted using missing categories for covariates and including only people with non-missing outcome information.

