We will use statistical analyses to address the risk of ME/CFS and other health conditions in those with versus without SARS-CoV-2 infection as risk difference or risk ratios or odds ratios, as appropriate. We will also adjust for additional patient-level factors of interest, including age, sex, race/ethnicity, income, and presence of specific underlying conditions such as hypertension and diabetes. We anticipate that as more is learned about the clinical courses of persons with symptomatic SARS-CoV-2 infection, additional covariates of interest available from electronic record data will be assessed for their association with adverse outcomes.

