## 3.17. Safety/harms

Study risks are related to invasion of privacy and potential breach in confidentiality. Data maintained at the research site will include minimum necessary information and will be secured according to institution standards. Data maintained by Hugo Health will be subject to their privacy security policies https://hugo.health/security), Privacy Notice (https://hugo.health/privacy-notice), Terms of Service (https://hugo.health/terms-of-service/). Participants may experience inconvenience of filling out electronic patient-reported outcome measure surveys, which should take up to 20 minutes for the longer surveys (at enrollment baseline), and 15 minutes for the weekly/monthly surveys.

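### Figure 1 schedules no patient-reported health status or preexisting-condition item at enrolment, which contradicts the baseline comparison planned in Section 3.9.1

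*Protocol*

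**What the plan says.** Section 3.14, Figure 1, has one assessment row marked at enrolment: "Age, gender, symptoms of SARS-COV-2 infection, recent health care use, social determinants of health | X".

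The outcome row, which includes "physical and mental health (PROMIS-29), cognitive SF-8, hospital-free survival" and also exercise and work and activity status, ends "myalgic encephalomyelitis/chronic fatigue syndrome | | X | X | X | X | X | X | X". Its time-0 cell is empty and its first mark is at 3 months. The row for comorbidity reads "Preexisting conditions | | X | X | X | X | | | X".

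The analysis text in Section 3.9.1 plans to "Compare health status at baseline and follow-up between persons in the same age group who test SARS-CoV-2 positive and negative at initial test". The same list of analyses describes patient-reported health status as cognition, physical health, mental health and return to work. Section 3.9.1 also plans to adjust for "presence of specific underlying conditions such as hypertension and diabetes".

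Section 3.17, on participant burden, refers to surveys "which should take up to 20 minutes for the longer surveys (at enrollment baseline". It does not say what that enrolment survey contains.

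**The concern.** This is a non-randomised cohort in which symptomatic test-negative people serve as controls for symptomatic test-positive people. Its inference depends on showing how the two groups compare at the start and on adjusting for conditions that preceded the infection. If the schedule is followed as printed, no PROMIS-29, cognition, exercise or work-status value exists at the start.

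Self-reported comorbidity has a related problem. It is first asked well after the test and then asked again through 12 months and at close-out, with no stated rule for which answer defines a preexisting condition. In a study of sequelae, a condition diagnosed after infection may be an outcome rather than a confounder.

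This is more than detail left to a statistical analysis plan, because an analysis plan cannot supply enrolment data that were never collected.

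**Working it through.** **Reading the schedule.** Each row of Figure 1 was split at its cell boundaries and matched to the timepoint header. The cells line up, so the blanks are not an artefact of table extraction.

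| Row | 0 | 3 | 6 | 9 | 12 | 15 | 18 | Close-out |
|---|---|---|---|---|---|---|---|---|
| Demographics, symptoms, recent care use, social determinants | X | | | | | | | |
| Outcomes (PROMIS-29, cognition, exercise, work status and others) | | X | X | X | X | X | X | X |
| Preexisting conditions | | X | X | X | X | | | X |

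**Schedule against planned analysis.**
1. Section 3.9.1 needs health status at baseline by test result within age group.
2. The patient-reported components it lists are cognition, physical health, mental health and return to work.
3. All of these sit in the outcome row, which has no mark at time 0.
4. Available at enrolment are symptoms, recent care use, demographics and social determinants. These describe the groups but are not the listed health-status measures.

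**Can the 3-month survey stand in for baseline?** No. Section 3.5 gives PROMIS-29 a 7-day recall, apart from physical function and social participation, which specify no timeframe. A 3-month answer therefore does not recover the state at enrolment.

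**Timing of self-reported comorbidity.**
- Maximum gap from test to enrolment (Table 1): 42 days.
- First mark for preexisting conditions (Figure 1): 3 months, about 91 days after enrolment.
- Longest gap from test to first scheduled answer: 42 + 91 = 133 days, and 133 / 30.4 ≈ 4.4 months.
- Shortest gap, with enrolment on the day of the test: about 3 months.

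**Other comorbidity sources.** Section 3.6.1 has participants link their health portals at enrolment, yielding problems, diagnoses and clinical notes. Diagnoses dated before the test could define preexisting conditions for people with linked records. Section 3.9.1 does not name this source, a look-back period or a date cutoff. Section 3.6.1 also allows that some participants do not complete linkage at enrolment.

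**Which part is wrong?** Section 3.17 gives up to 20 minutes for the enrolment survey and 15 minutes for later ones, which suggests more enrolment content than the single marked row. Section 3.17 is weak evidence, however. It calls the later surveys weekly or monthly, whereas Section 3.6.1 sends surveys every 3 months. The instruments are assigned to Appendix A, which is not in the text at hand.

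**The case against.** The strongest reply is that Figure 1 may simply be incomplete. A longer enrolment survey is mentioned, and the health-status items may well be on it. This stands as a limit on the finding: the documents show that the schedule and the analysis text disagree, not that the data are missing in practice. It does not remove the need for a correction.

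Three stronger readings are tempting, and the documents do not support them.

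- A reader might infer that comorbidity adjustment necessarily rests on data recorded after infection. The portal link offers problems and diagnoses that may predate the test. Also, when an item is asked is not the period it refers to; the row is labelled as preexisting, and its wording is not shown.
- A reader might infer that anyone who misses the 3-month survey has no self-reported comorbidity at all. The item is marked again at 6, 9 and 12 months and at close-out, so only someone who misses all five occasions lacks it. Section 3.9.1 also says multiple imputation will be considered for missing covariates and plans a missing-category sensitivity analysis.
- A reader might infer that a time-0 PROMIS score would measure pre-infection health. Enrolment follows the test by up to 42 days in symptomatic people, so with 7-day recall the score reflects acute or recent illness. It would provide the baseline that Section 3.9.1 calls for, but not a pre-infection value.

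**Conclusion.** The contradiction is real. Under Figure 1 as printed, the planned baseline comparison has none of the patient-reported measures that Section 3.9.1 lists as health status, and the first self-reported comorbidity answer falls about 3 to 4.4 months after the test. The upper figure assumes enrolment on day 42 and a 3-month survey sent on time; a late response would lengthen it.

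No size of bias can be given. That would need the rate of new diagnoses in each group, the extent of portal linkage and the wording of the item, none of which the documents state.

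The point should be fixed before the analysis is relied on. Confidence is medium, because the enrolment survey may already contain these items, in which case the error is confined to Figure 1. It does not show that the study's adjustment is invalid.

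**What to change.** - **Figure 1:** mark time 0 for PROMIS-29, cognitive SF-8, exercise, work status and preexisting conditions, the last worded as present before the illness that led to the test. If these items are already on the enrolment survey, correct Figure 1 to show them and make Section 3.17 agree.
- **Section 3.9.1, adjustment:** adjust only for conditions present before the index test, taken from the enrolment item and from portal diagnoses dated before that test. State that later diagnoses do not count as preexisting, and say what applies when records are not linked.
- **Section 3.9.1, baseline:** describe the time-0 PROMIS score as an enrolment value taken during or soon after acute illness, not as pre-infection health.

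The cost is a table correction, a few sentences and, if the items are new, a slightly longer first survey. For people already enrolled without these items, portal diagnoses dated before the test can still define comorbidity, but an enrolment PROMIS or cognition score cannot be recovered. The baseline comparison would then be limited to those who have one.

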## 3.15. Allocation

Not applicable.

## 3.16. Blinding (masking)

### 3.16.1. Blinding mechanism

Not Applicable.

## 3.17. Safety/harms

Study risks are related to invasion of privacy and potential breach in confidentiality. Data maintained at the research site will include minimum necessary information and will be secured according to institution standards. Data maintained by Hugo Health will be subject to their privacy security policies https://hugo.health/security), Privacy Notice (https://hugo.health/privacy-notice), Terms of Service (https://hugo.health/terms-of-service/). Participants may experience inconvenience of filling out electronic patient-reported outcome measure surveys, which should take up to 20 minutes for the longer surveys (at enrollment baseline), and 15 minutes for the weekly/monthly surveys.

## 3.18. Auditing

Not Applicable.

# 4. ETHICS AND DISSEMINATION

## 4.1. Research ethics approval

Ethics approval of this protocol has been obtained at each individual site including Rush University (protocol number: 20030902, approved 3/14/2020), Yale University (2000027976, approved 4/30/2020), the University of Washington (UW Human Subjects Division, STUDY00009920, approved 4/2/2020), Thomas Jefferson University (20p.1150, approved 1/21/2021), the University of Texas Southwestern Medical Center (STU 2020-1352, approved 2/3/2021), the University of Texas, Houston (HSC-MS-20-0981, approved 9/10/2020), the University of California, San Francisco (20-32222, approved 1/25/2021) and the University of California, Los Angeles (20-001683, approved 12/18/2020). The Yale University ethics approval includes the role as the analytic lead. Additionally, the Rush University ethics approval includes INSPIRE data storage on the Hugo platform and transfer of data to Rush for secure storage.

## 4.2. Protocol amendments

Listed in Appendix A on Page 2 (uploaded with manuscript submission as supported information).

## 4.3. Informed consent process

This study involves self-enrollment with an online consent process using an electronic consent form designed with easy-to-read language. The consent form is a click-through digital document where, after reading the document, the participant clicks to agree or disagree to study participation. Electronic consent occurs through the Hugo platform.

## 4.4. Confidentiality

Privacy concerns pertaining to the use of the Hugo platform will be directed to Hugo and their privacy policies.

Subjects may feel that participating in this study is an invasion of their privacy. Subjects choose to share their personal health records with the study team. This will be outlined in the consent form and explained during any phone-based communications. Some subjects may feel a violation of privacy if they are directly contacted by the study team and ask to participate in the study. We will explain how patient information is obtained and why the patient is being approached about this study.

Self-reports of information shared via the Hugo platform for research will also be stored in the patient’s Hugo account along with the patients PHR data. This information will remain in their account unless directed by the participant to delete it. This information is explained in the Hugo terms and services and in the study consent form.

## 4.5. Declaration of interests

The Innovative Support for Patients with SARS-COV-2 Infections (INSPIRE) Registry is funded by the Centers for Disease Control and Prevention (CDC), National Center of Immunization and Respiratory Diseases (NCIRD) (contract number: 75D30120C08008; co-PIs [name], and [name]). Partners from the CDC assisted with study design, the preparation of this protocol manuscript and the decision to publish this manuscript. The findings and conclusions in this report are those of the authors and do not necessarily represent the official position of the Centers for Disease Control and Prevention (CDC). No others sponsors or funders (other than the named authors) played any role in the study design, data collection and analysis, decision to publish, or preparation of the manuscript.


**COMPETING INTERESTS**

I read the journal's policy and the authors of this manuscript have the following competing interests: [name] is co-founder for HugoHealth.

## 4.6. Access to data

The final data set will be accessible by study investigators, the CDC funders, and others as permitted contractually by the CDC.

## 4.7. Dissemination policy

### 4.7.1. Trial results

Research findings will be disseminated through presentations to international audiences as well as through publications in peer-reviewed journals.

## 5.2. Funders

Centers for Disease Control and Prevention

### 5.3.2. Sponsor and funder

The study sponsor and funders provided periodic advice about study design; collection, management, analysis, and interpretation of data; writing of the report; and the decision to submit the report for publication, but they do not have ultimate authority over any of these activities.

### 5.3.3. Trial committees

The administrative core (Rush) oversees the primary contract with the sponsor, subcontracts with the clinical core (University of Washington [UW]) and the analytic core (Yale University), and three vanguard enrolling sites (Rush, UW, Yale) as well as the data software vendor (Hugo Health LLC, Guilford, CT).

The clinical core (UW) oversees monitoring and improvement of enrollment and retention at all sites (above, Thomas Jefferson University, University of California San Francisco, University of California Los Angeles, University of Texas Southwestern, University of Texas Houston).

The analytic core (Yale) oversees data analysis and reporting.

The study has a decision-making executive committee, an advisory steering committee, and a publications committee.

# 6. APPENDICES

## 6.1. Informed consent materials
